##### Costs

In this study we include direct costs of the intervention and COPD care. Intervention costs include development costs of the patient platform and costs of the implementation process. Development costs are provided retrospectively by the owner of the portal. Implementation costs are administered by the research group and mainly include costs of home visits and interviews by telephone. The cost for COPD care (time of professional care) is extracted from the portal in which consultation in general practice will be registered in an agenda. In addition, hospitalisation (caused by COPD exacerbation) will be based on reports of the patient and practice nurse in the portal. All costs are based on regular tariffs in Dutch healthcare.

#### Determinants

##### Self-efficacy

Self-efficacy is measured using the Generalized Self-Efficacy Scale (GSES), which will be displayed at baseline. This 10-item questionnaire was designed in 1981 by Schwarzer [35]. The items are scored on a four-point scale, in which a higher score reflects higher self-efficacy. Research in 28 countries showed that Cronbach’s alpha varies between .76 and .90, of which mostly above .80. Self-efficacy is derived from the Social Cognitive Theory, which states that behavioral change is made possible by personal sense of control. Self-efficacy is the “belief in one’s capabilities to organise and execute the courses of action required to produce given attainments”. Research shows that self-efficacy is an important factor for self-management in behavioral change of the chronic ill, such as diabetics and cardiovascular patients. For example, in people with type 2 diabetes self-efficacy is an important factor influencing self-management behaviours; self-efficacy impacts adherence to treatment [36].

##### Sociodemographic characteristics

These are assessed by a purpose-designed online questionnaire. We include the following characteristics: age, socioeconomic status, marital status, and general use of online and digital products and services. Since decreased access to internet and decreased general health outcomes have been associated with lower socioeconomic status, minority racial/ethnic groups, older age, and poorer health we will include these characteristics in our study.

### Power calculation

Health status of patients with COPD generally decreases over time. Recent research on disease management programs in COPD in primary care shows that a general increase of 1.5 to 2.0 points (SD 0.75) in CCQ can be expected during a one year period [37]. In our study we offer patients a web portal in addition to their regular disease management program. We therefore expect that the regular deterioration in CCQ (from 1.5 to 2.0 points) will change to stabilisation of health status at 1.5 CCQ points. Hence, we expect a significant difference in health status of 0.5 points in patients using the portal (2.0-1.5 = 0.5 points). To measure significant differences in health status (>0.5 CCQ points) at 80 % power, SD 0.75 and *α* = 0.05, 37 patients must be included. Based on an estimated 20 % drop-out during the study, 45 (37/0.80) patients are needed. As we use two different organisational implementation methods within two of the care groups 2*45 = 90 patients must be included in those settings. In the third care group only one organisational implementation method (free use) is used. Hence, a total of 225 (90 + 90 + 45) patients are necessary to achieve sufficient statistical power.

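### The drop-out inflation is miscalculated: 37/0.80 is 46.25, so the plan's own rule gives 47 per arm and 235 in total, not 45 and 225

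*Protocol article*

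**What the plan says.** The whole calculation stands in the Power calculation section of the protocol article.

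- **Effect and spread.** The authors state that "we expect a significant difference in health status of 0.5 points in patients using the portal", with an SD of 0.75.
- **Base size.** The design values are given as "at 80 % power, SD 0.75 and" a significance level of 0.05, leading to "0.05, 37 patients must be included".
- **Drop-out.** "Based on an estimated 20 % drop-out during the study", the section continues, "45 (37/0.80) patients are needed".
- **Care groups 1 and 2.** Each has two implementation methods, so "2*45 = 90 patients must be included in those settings".
- **Total.** With one further arm in care group 3, "a total of 225 (90 + 90 + 45) patients are necessary to achieve sufficient statistical power".

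No other section gives a different sample size or explains the 45.

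**The concern.** The section prints both an operation and its result, and the two disagree. The figure of 45 is the building block of the recruitment target: it enters five times and produces the 225 that the article calls necessary for sufficient power. If it is too low, a trial that recruits exactly to plan and loses exactly the expected share of patients ends below its own requirement in every arm. Readers will also judge completed recruitment against 225.

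**Working it through.** **Inputs**, all from the Power calculation section: difference 0.5 CCQ points, SD 0.75, power 80 %, alpha 0.05, base size 37, drop-out 20 %, and five arms (two in care group 1, two in care group 2, one in care group 3).

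**Step 1: reproduce the base size.** The section does not state the test or whether it is one- or two-sided. I assume a two-sided comparison of two independent means.

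- Normal approximation: n per group = 2 × [0.75 × (z₀.₉₇₅ + z₀.₈₀) / 0.5]² = 35.32, rounded up to 36.
- t-test (noncentral t): power is 79.7 % at 36 per group and 80.8 % at 37, so the smallest sufficient n is 37.

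The stated 37 is therefore reproduced by the two-sided two-sample t-test. Other readings do not give it: the one-sided two-sample normal approximation gives 28, and a one-sample or paired t-test with SD 0.75 gives 20.

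**Step 2: apply the drop-out.**

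- n enrolled = 37 / (1 − 0.20) = 37 / 0.80 = 46.25, rounded up to 47.
- The plan prints 45. Even rounding down would give 46.

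**Step 3: run the plan's figure backwards.**

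- 45 × 0.80 = 36 completers, one fewer than 37.
- 47 × 0.80 = 37.6, which meets the requirement.
- Drop-out at which 45 enrolled still leaves 37: 1 − 37/45 = 17.8 %, below the assumed 20 %.

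**Step 4: carry it to the total.**

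| | Plan | Plan's own rule |
|---|---|---|
| Per arm | 45 | 47 |
| Care group 1 (2 arms) | 90 | 94 |
| Care group 2 (2 arms) | 90 | 94 |
| Care group 3 (1 arm) | 45 | 47 |
| Total | 225 | 235 |

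The gap is 10 patients, and 10/225 = 4.4 %. If rounding is left to the total, 5 × 46.25 = 231.25, so 232, which is still above 225.

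**Step 5: effect on power with 36 completers per arm.** The two-sample t-test gives 79.7 %, against 80.8 % with 37. The normal approximation gives 80.7 %, against 81.8 % with 37. Either way the loss is about 1.1 percentage points.

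**The case against.** The strongest reply accepts that the division is wrong but disputes what follows from it.

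1. **The 45 may be right and something else misprinted.** 36/0.80 is exactly 45, and 36 is the normal-approximation size, so the slip could lie in the 37. Alternatively, 37 × 1.20 = 44.4 rounds up to 45. Neither is what the section prints. The first contradicts its stated 37. The second is not a valid inflation for 20 % loss, since it leaves 36. What stands is that the origin of the 45 is unknown, and that 37, 0.80 and 45 cannot all be kept.
2. **The power figure rests on an inferred test.** This stands. The section names no test, and the Methods/Design section describes a within-group interrupted time series. With 36 completers, power is 79.7 % (two-sample t), 80.7 % (two-sample normal approximation) or 97.3 % (one-sample or paired t, if 0.75 were the SD of change). Only the first falls below 80 %. It is, however, the standard calculation that yields the plan's 37. The arithmetic error does not depend on any of this.
3. **The consequence is slight.** This also stands. The miss is one completer per arm, the 20 % is itself an estimate, and the Data analysis section pools arms for the comparison of support levels (1a and 2a against 1b, 2b and 3: 90 against 135 enrolled), where one completer per arm hardly matters. That limits the weight of the point but does not make the printed figures correct.

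**Conclusion.** The concern holds. The printed quotient is wrong, and the error passes into the recruitment total. Taking the stated 37 and 20 % as given, and rounding up in each arm, the requirement is 47 per arm and 235 in total, 10 more than the stated 225. At 45 per arm the plan reaches 36 completers, not 37.

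The practical effect is small. On the two-sided two-sample t-test, power falls from 80.8 % to 79.7 %, just under the stated 80 %; on the normal approximation it stays just above. This is a correction to a figure that the trial relies on, not a serious loss of power. Whether a two-sample calculation suits the within-group time-series analysis is a separate question; the 37 is not challenged here.

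**What to change.** Correct the Power calculation section in one of two ways:

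- **Restate the target:** 37/0.80 = 46.25, so 47 per arm, 94 in each of care groups 1 and 2, 47 in care group 3, and 235 in total. This adds 10 patients.
- **Keep 225 and restate what it delivers:** 45 per arm leaves 36 completers at 20 % drop-out, with 79.7 % power for a 0.5-point difference under a two-sided two-sample t-test with SD 0.75; or 45 per arm leaves 37 completers if drop-out is no more than about 18 %. This needs no extra patients.

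In either case, name the test and its sidedness, so that the 37 and the power figure can be checked. If the base size was meant to be 36, say so and correct the 37. The cost is an edit to one section, plus 10 patients only if the first route is chosen.

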### Data analysis

Along with our research design, analyses will be multilevel:To investigate the effect of the use of the web portal on the primary clinical outcomes, the ITS data will be analysed. The preferred method to analyse ITS studies is a statistical comparison of time trends before and after the intervention. Time series analysis using ARIMA models is one way of analysing the data, but there are a number of statistical techniques that can be used depending on the characteristics of the data, the number of data points available and whether autocorrelation is present. The final choice for the method to analyse the data will be made when the total set of data is available after consultation of a statistician.To investigate the effects of organisational aspects uptake of the portal will be analysed for care group 1, 2 and 3 using Chi Square tests (Fishers’ Exact Test for categorical variables and *F*-tests for continuous variables) and (repeated measures) ANOVA analyses. To analyse the effects of organizational aspects as described in the paper, the groups will be compared.To investigate the effect of integration of the web portal in daily practice, outcomes within integrated (group 1 and 2) and the free use groups (group 3) will be analysed using Chi Square tests (Fishers’ Exact Test for categorical variables and *F*-tests for continuous variables) and (repeated measures) ANOVA analyses.To investigate the effect of different organisational implementation methods, outcomes within groups with high level support (1a and 2a) and low level support (1b, 2b and 3) will be analysed using Chi Square tests (Fishers’ Exact Test for categorical variables and *F*-tests for continuous variables) and (repeated measures) ANOVA analyses.To explore correlation between self efficacy, sociodemographic characteristics on the one hand and adoption of the portal and clinical outcomes on the other hand, Pearson product-moment coefficients will be calculated across all research groups.To make a cost-effectiveness analysis, the direct costs of the different organisational implementation methods will be defined and analysed parallel to the effects of the portal in terms of Quality of Life (EQ-5D).

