Because the most powerful studies are prospective studies, we chose a prospective parallel cohort design. We asked three primary care groups to invite their COPD patients for the e-Vita study. Because there are several differences between the groups (Fig. 3), we can not compare the COPD cohorts by combining data across three different groups. We chose for an interrupted time series (ITS) design to evaluate clinical outcomes (CCQ) within each group. In ITS studies, data are collected at multiple time points before and after an intervention in order to detect whether or not the intervention has a significantly greater effect than any underlying secular trend [26]. ITS can detect changes that are delayed or intermittent. It can also determine if the change is permanent or temporary. In addition, it allows evaluation of variables which are changing before the intervention, for instance, by comparing slopes of trend lines before and after the intervention. Finally, ITS makes it easier to control for confounding variables and regression to the mean [27]. The ITS will be performed according to guidelines of the EPOC Cochrane group [25]. Although well-conducted randomised trials provide the most reliable evidence on the effectiveness of interventions, they are not feasible for our setting of an implementation design with organisational changes in a real-life health care system within three different care groups with different demands. An advantage of an ITS design is that it allows for the statistical investigation of potential biases in the estimate of the effect of the intervention.

In addition to clinical outcomes, we also want to investigate the effect of different organisational implementation methods. Therefore we will implement the platform in group 1 and 2 using different methods. Differences will be measured using a parallel cohort design. To be certain that intervention groups will be balanced in known and unknown prognostic factors in the long run we will use randomisation within group 1 and 2. To rule out human influences we will randomise online for the level of support.

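### The primary CCQ trend is not tied to a patient-level analysis, so with 20% drop-out expected, selective loss could imitate or hide part of the expected stabilisation

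*Protocol article*

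**What the plan says.** - **Level of the comparison.** The opening text of Methods/Design says: "We chose for an interrupted time series (ITS) design to evaluate clinical outcomes (CCQ) within each group". It adds that data from the three care groups cannot be combined to compare the cohorts. Only the level of support is randomised, in groups 1 and 2, and every group is offered a portal.
- **Method.** Data analysis describes a comparison of time trends before and after the intervention. It then says "Time series analysis using ARIMA models is one way of analysing the data", notes that other techniques exist, and leaves the final choice until the complete data set is available and a statistician has been consulted. No other technique is named for this analysis.
- **Target.** In the Power calculation, the "regular deterioration in CCQ (from 1.5 to 2.0 points) will change to stabilisation of health status at 1.5 CCQ points". A higher CCQ is worse.
- **Drop-out.** "Based on an estimated 20 % drop-out during the study, 45 (37/0.80) patients are needed". This percentage is used only to enlarge the sample.
- **Collection.** Under Data collection, the questionnaires are built into the portal.
- **Selection check.** The check under Recruitment of patients and non-participation analysis compares participants with eligible non-participants. It does not compare leavers with stayers.

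**The concern.** An ARIMA analysis, as usually applied to such a design, works on one value per occasion, here the mean CCQ of a care group. If patients leave during follow-up, later means describe a different set of people from earlier means. When leaving is related to CCQ, the series moves without any change in any patient.

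The hoped-for result is a mean that stays at 1.5 instead of rising to 2.0. Loss of sicker patients pushes the later means down, in the same direction as that result. Equal loss in the support arms does not help, because the clinical effect is read within a group. There is also no portal-free series with the same loss against which to subtract it. Leaving the method open until the data are in means that the choice between occasion means and patient-level data, which can change the answer, is made with the results in view.

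**Working it through.** **The plan's own figure.** Inputs from the Power calculation: difference 0.5, SD 0.75, 80% power, α = 0.05 (two-sided assumed).
- Normal approximation: n = 2 × (1.960 + 0.842)² × 0.75² / 0.5² = 35.3 per group.
- Two-sample t-test: 36.3, so 37 per group, which matches the stated 37.
- The match is with a comparison of two independent groups, not with the within-group trend planned for CCQ.
- As a side point, 37/0.80 = 46.25, not 45.

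**Shift from selective loss, simple form.** Let a fraction d = 0.20 leave, and let leavers be D points worse than stayers. The full-cohort mean is 0.8 × stayers + 0.2 × leavers, so the stayers' mean lies 0.2 × D below it.

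| D (assumed) | Mean too low by | Share of 0.5 |
|---|---|---|
| 0.25 | 0.05 | 10% |
| 0.5 | 0.10 | 20% |
| 1.0 | 0.20 | 40% |

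With a negative D (healthier patients leave), the same shifts appear with the opposite sign.

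**Upper bound.** If CCQ is normal with SD 0.75 and exactly the worst 20% leave, the shift is 0.75 × φ(0.842)/0.8 = 0.26 points, or 52% of 0.5.

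**Simulation with no portal effect.**
- CCQ starts at 1.5 and rises 0.5 a year, with total SD 0.75 (assumed split: 0.65 between and 0.374 within patients).
- Occasions are at 0, 6, 12 and 18 months, from the 6-month intervals in Methods/Design. Data collection gives 16 months in total.
- A total of 20% leave, with the odds of leaving depending on the previous CCQ.

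| Odds ratio of leaving per SD of CCQ (assumed) | Last-occasion mean too low by | Slope from pooled available data | Slope from patient-level mixed model |
|---|---|---|---|
| 1.65 | 0.06 | not run | not run |
| 2.7 | 0.11 | 0.43 | 0.50 |
| 7.4 | 0.16 | 0.40 | 0.51 |

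The true slope is 0.50 a year. Ignoring the patient level loses 0.07 to 0.10 of it (14% to 20%); the mixed model recovers it. The simulation has one straight trend and no pre-portal segment. It therefore shows the mechanism and its order of size, not the exact bias of the planned before/after contrast.

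**The case against.** The strongest objection is that the article fixes no faulty analysis. ARIMA is offered as one possibility, a statistician is to be consulted, and nothing says that patient-level data will be reduced to occasion means. Details of drop-out handling may sit in an analysis plan that is not shown. This stands in part. The absence of a missing-data section is no finding, and the bias arises only if means of available patients are used. What remains is something the article does state: the method for the primary outcome will be picked after the data are complete, and the only named candidate is one usually applied to group means. The section calls its analyses multilevel, but the list that follows sets out levels of research question and names no hierarchical model.

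A second objection concerns direction, and it also stands. No passage says that leavers are sicker. Terminally ill and immobile patients are excluded at entry (Participants), and the Discussion says that primary care patients have a low burden of disease. Because CCQs are collected in the portal, patients who feel well may be the ones who stop.

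A third objection is that each group's earlier trend is a comparator, so the design is not uncontrolled. That is right, but an earlier trend cannot remove the effect of loss that occurs later. How much loss falls after the portal starts is not stated; the drop-out is only placed during the study.

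A reader might infer that the primary result is biased in favour of the portal. The documents do not support this, because neither the use of occasion means nor the direction of loss is stated.

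**Conclusion.** The point holds as a conditional weakness. The plan leaves open, until the data are in, a choice that matters once 20% of patients are lost. If occasion means are used and leavers are 0.25 to 1.0 points worse than stayers, the later mean is 0.05 to 0.20 points too low. That is 10% to 40% of the 0.5-point target, with 0.26 points (52%) as the bound, so the artefact could imitate part of the expected stabilisation but not all of it. If healthier patients leave, the error works against the portal. The SD, target and drop-out rate are the article's; the degree and direction of selection are assumptions. This is a cheap improvement that should be made, not evidence that the planned result is wrong.

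**What to change.** In Data analysis, state before the data are seen that the primary before/after CCQ trend in each care group is estimated at patient level and not from occasion means. The model would be a segmented mixed model with patient-specific intercept and slope, using all available CCQs.

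This model assumes that drop-out depends on CCQ values already observed; it does not protect against loss driven by unrecorded worsening. So add one sensitivity analysis in which patients who drop out continue to worsen at 0.5 points a year, the rate implied by the Power calculation (1.5 to 2.0 over one year). A table of T1 and last CCQ by later drop-out would be useful, optional support, because it would show which way the loss runs.

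The cost is plan wording and slightly more analysis work, with no new data. The estimated stabilisation may look less favourable than one from occasion means.

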## Background

Chronic obstructive pulmonary disease (COPD) represents one of the main causes of morbidity and mortality, and worldwide nearly 3 million people die from COPD every year [1]. In the Netherlands, COPD was responsible for almost 5 % of the total deaths in 2011 [2]. More than 3 million people died worldwide of COPD in 2012, which is equal to 6 % of all deaths globally that year [3]. COPD is a highly complex disease to manage as patients show great variation in symptoms and limitations in daily life. This results in a position in the top ten of most expensive diseases for respiratory disease [2]. Within the last decade self-management support of COPD has been introduced as an effective method to improve quality and efficiency of care, and to reduce healthcare costs [4–6]. It has shown to improve the level of recognition of severe exacerbations [7]. Interventions to support self-management have shown reductions in hospital admissions and fewer sick days as a result of exacerbations [8, 9]. Studies have shown that eHealth interventions are effective in stimulating self-management. Patients are better able to cope with their illness at the time and place of their choosing, allowing them to adapt their lifestyle to their condition while eHealth support also reduces medical staff consultations [10]. The deployment of eHealth applications facilitates accessibility to healthcare, which in turn enhances the patients’ understanding of their disease, sense of control, and willingness to engage in self-management [11, 12]. Although patients’ attitudes and receptiveness towards eHealth applications are promising in certain groups of age and education [13–15], large-scale adoption of eHealth in daily practice is low. Despite the urge to change the organisation of health care and the potential of eHealth to support this, large-scale implementation in daily practice remains behind on predictions, especially in the Netherlands [16].

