In this study we combine different study methods within one research to investigate organisational implementation methods and net benefits of eHealth interventions from human, organisational, and technical view. To do so, we created a unique study that enables us to simultaneously investigate clinical effects, as well as effects of different organisational implementation methods whilst controlling for confounding effects on an organizational level. In Fig. 2 the combined study design is shown.

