**Fig. 2 Fig2:**
[figure not shown]
Research design for the different groups and interventions of e-Vita COPD

Organisational and technical differences are depicted in Fig. 2: three different care groups and two different web portals are included. Two different methods of implementation are distinguished within group 1 and 2: one with high level of personal assistance and one with low level of personal assistance. All patients in group 1 and 2 start with a personal instruction by the primary care nurse during a regular control visit. Patients will be randomly subdivided in two groups by computer by research assistants (randomisation is computerised to prevent human influence) with high (a) and low (b) level of support. In group 1a, high level support implies home visits for patients by a research nurse who accompanies the use of the web portal. In group 2a, high level support implies telephone consultation for patients by a research nurse who accompanies use of the web portal. In group 1b and 2b low level support implies that the primary care nurse shows the patient only once how to use the web portal (the usual organisational implementation method in daily practice) without any follow-up instruction. In group 3 the web portal is offered as free use: patients will receive instructions from the web portal itself. There will be no active support from caregivers or research nurses.

The groups differ in organisation, area, use of the web portal, and integration of the portal in a COPD disease management program (Fig. 3); these characteristics are based on Dutch reports of care groups [28]:

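### The non-randomised care-group and integration comparisons are assigned tests without covariates, so differences in patient case mix could be credited to organisation or integration

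*Protocol article*

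**What the plan says.** Methods/Design limits randomisation to the support level: "we will use randomisation within group 1 and 2". Care group itself is not randomised. The text after Fig. 2 says "The groups differ in organisation, area, use of the web portal" and adds integration in the disease management programme as a further difference. Methods/Design also says the cohorts cannot be compared by pooling data over the three groups. The recruitment section accepts that volunteering by practices and patients may cause bias.

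The Data analysis section then names tests for two comparisons between care groups:

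- Care groups: "uptake of the portal will be analysed for care group 1, 2 and 3 using Chi Square tests", followed by Fisher, F-tests and (repeated measures) ANOVA.
- Integration: "outcomes within integrated (group 1 and 2) and the free use groups (group 3) will be analysed using Chi Square tests", with the same list.

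The patient characteristics collected are "age, socioeconomic status, marital status, and general use of online and digital products and services", together with self-efficacy (GSES) at baseline and the CCQ from T1 onwards. Their one stated use as explanatory variables is a set of Pearson coefficients over all groups. Methods/Design describes the study as able to investigate "effects of different organisational implementation methods whilst controlling for confounding effects on an organizational level". The Abstract and the Discussion make similar statements.

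**The concern.** Chi-square tests, F-tests and ANOVA without covariates compare groups as they stand. That is adequate after randomisation. Here the groups come from different areas and organisations, and practices and patients chose to join.

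The article itself gives reasons to expect that case mix matters. The Background says that patients' "receptiveness towards eHealth applications are promising in certain groups of age and education". The section on sociodemographic characteristics links socioeconomic status, ethnicity, age and poorer health to internet access and general health, and gives this as the reason for collecting them.

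If one care group has older or less digitally active patients, its lower uptake or worse scores could be read as the result of its organisation or of a portal that is not integrated. The best organisational implementation method is a stated aim, and these comparisons feed that conclusion.

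**Working it through.** **1. Is the choice of test stated or left open?** The Data analysis section postpones the method only for the interrupted time series (ITS), to be settled with a statistician once the data are complete. For the care-group and integration comparisons it names the tests. The section calls its analyses multilevel, but the word introduces a list of separate analyses and specifies no adjusted model.

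**2. Group sizes.** The power calculation gives 37 per group. A two-sample t-test with difference 0.5, SD 0.75, two-sided alpha 0.05 and 80% power needs 36.3, rounded up to 37, so this reproduces. The article plans 45 per (sub)group after drop-out, hence 90 + 90 + 45 = 225. Group 1 v 2 is 90 v 90, group 1 or 2 v 3 is 90 v 45, and integrated v free use is 180 v 45.

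**3. Assumptions (none is in the article).** There is no true care-group effect. Uptake is 60% in habitual internet users and 30% in others. The share of habitual users differs between groups.

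**4. Spurious difference.** Uptake in a group with share *q* is 0.60*q* + 0.30(1 − *q*).

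- Shares 70% v 50%: 0.51 v 0.45, a difference of 6 points.
- Shares 80% v 40%: 0.54 v 0.42, a difference of 12 points.

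**5. Chance of a false positive.** With difference *d* and pooled uptake *p*, the crude test rejects with probability about Φ((*d* − 1.96·SE0)/SE1) + Φ((−*d* − 1.96·SE0)/SE1). Here SE0 = √[*p*(1 − *p*)(1/*n*1 + 1/*n*2)] and SE1 = √[*p*1(1 − *p*1)/*n*1 + *p*2(1 − *p*2)/*n*2].

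For 180 v 45 and the 12-point case, *p* = (180 × 0.54 + 45 × 0.42)/225 = 0.516, SE0 = 0.0833 and SE1 = 0.0824. The result is 0.300. For the 6-point case, *p* = 0.498, SE0 = 0.0833 and SE1 = 0.0830, giving 0.110.

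Simulation (3,000 trials per setting) agrees:

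| Sizes | 70% v 50% | 80% v 40% |
|---|---|---|
| 90 v 90 | 11.5% | 35.5% |
| 180 v 45 | 10.7% | 30.0% |
| 90 v 45 | 9.7% | 25.3% |

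A logistic model that includes the one factor rejects in 4.6-5.2%.

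**6. Dependence on the assumptions.** With equal shares the crude test stays at 5%. For 180 v 45, uptake of 60% v 40% by factor and shares of 60% v 40% give about 8%. Uptake of 80% v 20% and shares of 70% v 30% give about 83%. A test stratified on the factor stayed at 4.8-5.2% in the settings simulated. Adjustment restores 5% in these examples because the only confounder is the one adjusted for.

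**The case against.** The strongest reply is that a condensed article need not list covariates, that it never rules them out, and that ANOVA can take them. This has some force for the scores. It has little for uptake, where a chi-square or Fisher test has no place for a covariate, and the article gives the collected characteristics a different role.

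Several stronger readings are tempting but not supported:

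- **That the plan claims to control case mix and then does not.** The Abstract, Methods/Design and Discussion claim control of organisational confounding only. What does stand is that no test named for these comparisons controls organisational confounding either.
- **That no analysis in the study adjusts for anything.** The ITS method is open, and the ITS runs within each care group, so differences between care groups do not enter the primary clinical analysis.
- **That these characteristics are known to drive portal use.** The article links them to internet access, general health and, for age and education, receptiveness. Patients without internet access are excluded, which closes part of that route.
- **That bias will occur.** The imbalance is unknown, so it could occur.

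Two practical objections also stand. The questionnaires sit in the portal, and for non-participants only CCQ, gender and age are promised. Covariates may therefore be missing mainly in patients who never take the portal up. In addition, adjustment for patient characteristics cannot separate integration from area, portal version, caregiver training or programme history.

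**Conclusion.** The point holds in a limited form. For two non-randomised comparisons the article states tests without covariates, although it acknowledges that the groups differ, accepts possible volunteer bias and collects relevant patient data. Case mix could then be taken for an effect of organisation or integration.

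The 10-36% false-positive range illustrates the mechanism under the assumed uptake rates and imbalances. It is not an estimate for this study. It assumes one binary factor, complete covariates and no true group effect.

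The primary ITS analysis and the randomised a-versus-b contrast inside groups 1 and 2 are not touched. The planned support contrast, "outcomes within groups with high level support (1a and 2a) and low level support (1b, 2b and 3) will be analysed", does pool the non-randomised group 3 with the low-support arms and shares the weakness to that extent. The point concerns secondary comparisons, but the remedy is cheap enough that it should be adopted.

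**What to change.** 1. Make covariate-adjusted regression the main analysis of the care-group and integration comparisons among enrolled participants: logistic for uptake, a count model for log-file use, and linear regression or ANCOVA for scores. Fix the covariates in advance: age, socioeconomic status, general digital use, GSES and T1 CCQ (as the baseline value). Show the crude result alongside.
2. Where portal-based covariates are missing for patients who never log in, adjust uptake for what is available for all, for example age, gender and CCQ. Report the missingness by group and by uptake.
3. Describe both contrasts as associations, because care group coincides with area, portal version, training and programme history.
4. Narrow the statements on control of organisational confounding in the Abstract, Methods/Design and Discussion. Adjustment for patient characteristics does not deliver that control.

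The cost is a change of wording, somewhat more analysis work, some loss of patients or covariates to missing data, and a more modest claim. No extra patients or measurements are needed.
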